### Power analysis

The sample size was determined by means of a power analysis. To detect a clinically significant impact (average effect size (Cohen's d) ≥ 0. 6) on the primary outcome variable (number of patients remain in care with an alpha of 0. 05 and a power of 0.85), we needed at least 50 patients per condition. In another ACT trial, Sytema et al [48] found 20% lose for randomization due to patients' failure to meet the inclusion criteria, and patients who refused to give informed consent for the interview [48]. We therefore wanted to include 80 patients in the ACTE team and 80 patients in the CAU condition. This will be enough to prove a clinically significant effect.

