### Statistical analysis

Analyses will be performed according to the *intention to treat *principle, which means that everyone who is randomized stays in the group in which they were randomized. Statistical package for the social sciences, version 15.0 will be used to analyze the data. The primary outcome measure is the differences between ACTE and CAU regarding the number of patients who were out-of-contact with mental health services. Secondary outcome measures are improvement of psychosocial functioning (total HoNOS 65+ score, total score from baseline to the final interview after 18 months), need-for-care over time (primary outcome measures), the number of crisis contacts and (in)voluntary admissions, and the number of admission days (these last 3 measures will be retrieved from administration files) The interviewer collects the other secondary outcome measures (subjective quality of life and client satisfaction.) Categorical variables shall be analyzed using chi-square tests. Mixed models with repeated measurement were applied for the continuous outcomes. This model will be used because of the ability to include participants with missing data. Missing data at the second and third interview will be imputed with the last carried out interview.

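### Carrying the last interview forward defeats the reason given for the mixed model and can bias the interview outcomes in either direction

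*Protocol article*

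**What the plan says.** Three consecutive sentences of the Statistical analysis section matter. The model: "Mixed models with repeated measurement were applied for the continuous outcomes". The reason: "This model will be used because of the ability to include participants with missing data". The rule for gaps: "Missing data at the second and third interview will be imputed with the last carried out interview". The section names no other method for missing interviews and no sensitivity analysis, and no other section withdraws the rule. Analysis is by intention to treat, "which means that everyone who is randomized stays in the group in which they were randomized".

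Other sections bear on how many interviews will be missing, and in which arm:

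- The first item under Hypotheses is that fewer ACTE patients will drop out of care.
- Table 1 says that CAU usually discharges patients who refuse contact or do not attend.
- The Discussion says the assessor can reach these patients only through their clinicians.
- Procedure lets the assessor rate from the records, or by asking the clinician, when a patient will not answer.
- The Discussion reports five deaths by 1 August 2010, three in the intervention group and two in the control group.

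**The concern.** A mixed model fitted by likelihood uses every interview that took place and needs no filled-in values. It is valid if missingness depends only on observed data. Carrying the last interview forward replaces that assumption with a stronger one: that a patient's score stays where it was last seen. The model then treats the copy as a measurement.

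If patients change over time and the arms lose interviews at different rates, the arm with more gaps is held closer to its early scores. Part of the common time trend then appears as a treatment difference, or part of a real difference disappears. Unequal loss is plausible here, because keeping patients in contact is what ACTE is meant to change. The outcomes exposed are the interview measures. Psychiatric, somatic and social functioning is listed as primary in the abstract, Hypotheses and Outcomes sections, whereas Statistical analysis calls HoNOS 65+ secondary.

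**Working it through.** **1. The plan's own figure.** Inputs from Power analysis: "average effect size (Cohen's d) ≥ 0. 6", "with an alpha of 0. 05 and a power of 0.85", "we needed at least 50 patients per condition". Two-sided, n per arm = 2(1.960 + 1.036)² / 0.6² = 2 × 8.98 / 0.36 = 49.9, so 50. It reproduces (51 with the t distribution). Enrolment was 64, or about 32 per arm.

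**2. What the documents do not give.** There is no missingness rate at 9 or 18 months and no expected time trend. The 20% in Power analysis ("found 20% lose for randomization due to patients' failure to meet the inclusion criteria", together with refusals of the interview) is loss around entry, not follow-up loss. Every rate and trend below is therefore an assumption.

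**3. Bias formula.** Let p be the proportion of an arm missing at 18 months, Δ its mean change from baseline to 18 months, and f the average share of Δ that falls after a missing patient's last interview. The carry-forward mean at 18 months is the true mean minus p·f·Δ. With a common Δ and no true effect, the false ACTE − CAU difference is

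f · Δ · (p_CAU − p_ACTE).

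If half the change has occurred by 9 months, f lies between 0.5 (all loss after 9 months) and 1 (all loss before). With 50% against 20% missing and Δ of 0.6 SD in size, the false difference is between 0.30 × 0.6 × 0.5 = 0.09 SD and 0.30 × 0.6 × 1 = 0.18 SD. On HoNOS 65+ a lower score is better, so it favours ACTE if both arms improve and CAU if both worsen.

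**4. Simulation.** Standardized outcome, three visits, exchangeable correlation 0.6, monotone missing-at-random loss, 1,500 runs per scenario. A baseline-adjusted 18-month comparison after carry-forward stood in for the mixed model on filled data. A factored-likelihood fit to observed data stood in for the mixed model without filling. Results at 32 per arm:

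| Scenario | Missing CAU / ACTE | Carry-forward estimate |
|---|---|---|
| No effect | equal | about 0, rejection 4–5% |
| No effect, both improve 0.6 | 50% / 20% | −0.17, rejection 14% |
| No effect, both worsen 0.6 | 50% / 20% | +0.11, rejection 10% |
| Effect −0.6 | 20% / 20% | about −0.50 |
| Effect −0.6 | 40% / 40% | about −0.40 |
| Effect −0.6, CAU worsens 0.6 | 50% / 20% | −0.39 |
| Effect −0.6, CAU flat | 50% / 20% | −0.53 |
| Effect −0.6, CAU improves 0.3 | 50% / 20% | −0.61 |

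The observed-data fit gave −0.59 to −0.61 wherever the true effect was −0.6, and stayed within about 0.01 of zero under no effect. At 50 per arm the 14% and 10% become 19% and 13%.

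**5. Formula against simulation.** At 50 per arm with 50% / 20% missing and no effect, the estimate was −0.033 with no trend and +0.112 with both arms worsening. The trend part is 0.112 + 0.033 = 0.145, so f = 0.145 / (0.30 × 0.6) ≈ 0.8. The −0.03 arises because loss depends on earlier scores. Then 0.8 × 0.18 ≈ 0.14, and −0.14 − 0.03 = −0.17, while +0.14 − 0.03 = +0.11, as in the table.

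**6. A milder case in HoNOS points.** A second simulation used 4,000 trials, 32 per arm, intercept and residual SD 4.2 each (total √(4.2² + 4.2²) = 5.9), no effect, and both arms improving by 3 points at 9 months and 4 at 18. With 20% missing in ACTE and 40% in CAU, the false ACTE advantage was 0.44 points (0.44 / 5.9 ≈ 0.07 SD) with 6.0% rejection. With 10% against 50% it was 0.94 points and 10.3%. With 20% in both arms it was 0.0 and 4.5%.

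**7. Precision.** At 32 per arm with no effect, the carry-forward standard error was 0.18–0.20 against 0.22–0.27 for the observed-data fit, about 9% to 31% smaller. With 40% missing and no trend it was 0.181, below the 0.199 obtained with no data missing at all. Losing interviews cannot add information, so copies are being counted as data.

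**The case against.** **Direction.** A reader might infer that the rule manufactures an ACTE benefit. That requires patients to improve and CAU to lose more interviews. The Background expects the opposite course, deterioration after leaving care. Carry-forward would then hold CAU leavers at their better early scores and work against ACTE. The documents support bias either way, not a predicted sign.

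**Amount of missing data.** Dropping out of care is not the same as a missing interview, and the fallback in Procedure would supply some HoNOS and CANE ratings. This stands, and rates such as 50% are illustrations. The fallback is weaker once a patient has been discharged, and it cannot readily supply subjective quality of life or satisfaction.

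**Contradiction.** One might call the two sentences strictly contradictory. They are not: a patient with no earlier interview has nothing to carry forward, so the model can still meet incomplete records.

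**Standard errors.** One might infer that small standard errors alone cause false positives. They do not: with equal missingness and no effect, rejection stayed near 5%, and the carry-forward standard error matched the sampling spread of its own estimate. The excess rejections come from bias.

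**Deaths.** The article does not say how deaths are handled. Scoring after death follows only from the general wording, some of the five may have completed their interviews, and the 3 to 2 split does not suggest heavier loss in CAU.

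**Conclusion.** The point holds as a flaw in a stated method. For every patient with an earlier interview, carry-forward cancels the advantage for which the model was chosen, enters unobserved no-change values and, read literally, does so after death. The bias can create, shrink or by chance preserve a difference. Under 50% against 20% missing and a common 0.6 SD trend, the false difference is −0.17 or +0.11 SD with 14% or 10% rejection at 32 per arm. With milder imbalance (40% against 20%) it was about 0.07 SD and 6%. A true −0.6 fell to as little as −0.39. All of these figures rest on assumed rates, trends and correlation.

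A reader might also infer that the whole trial result is at risk. The documents do not support that: being out of contact, which Statistical analysis names as the primary outcome, comes from the registration system, as do crisis contacts and admissions, and the rule does not touch them. The point should be fixed before the interview outcomes are analysed.

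**What to change.** Delete the carry-forward sentence and put in its place:

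- Fit the repeated-measures mixed model by REML to the interviews actually obtained, with arm, categorical visit and their interaction.
- Impute nothing after death, and report deaths by arm beside the result.
- Add one sensitivity analysis for data not missing at random, for example multiple imputation with a delta shift that can differ by arm.
- Keep carry-forward, if at all, as a labelled sensitivity analysis.
- Report missing interviews by arm and visit, and how many ratings came from records or the clinician.

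The cost is small: one sentence replaced, the chosen model kept, and no new data collected. The timelines section places data analysis from 1 March 2012. It should be checked whether the named software version can run the delta-adjusted imputation.

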### Ethical considerations

Because the patients included in the study are difficult to engage, they will be allocated randomly over the two conditions without asking informed consent. This Zelen design [24] and the execution of this study were approved by the Dutch union of medical-ethic trial committees for mental health organizations. Data will be processed anonymously. Confidential information and patient names will be treated according to the medical confidentiality rules. All personal details will be awarded a code to which only the research team has the key.

### Research procedures & timelines

This study will proceed in four stages:

a. Preparation for data collection (1 March 2008 to 1 July 2008)

b. Inclusion of patients (1 July 2008 to 1 August 2010)

c. Follow-up (1 April 2009 to 1 March 2012)

d. Data-analysis, publication of articles, knowledge transfer, and writing of a thesis (1 March 2012 to 1 March 2013).

## Discussion

The central research question in this study is whether ACTE can ensure that elderly people with SMI remain in care and whether ACTE can reduce psychosocial symptoms and unmet needs more than CAU. Other research questions include whether the intervention can reduce the number of crisis contacts, reduce the number and duration of voluntary and involuntary admissions, and improve quality of life and client satisfaction.

This study will thus provide opportunities to examine how well ACTE works in practice with this group of elderly people, and whether it has any extra value over CAU. By helping to increase overall understanding of various forms of mental healthcare, its implementation may lead to an evidence-based intervention for this special group. If ACTE is shown to have added value, it can be implemented, and further research can follow.

The study results will be prepared for national and international publication and for presentation at national and international conferences. They may also lead to the publication of a handbook on ACT for the elderly.

This study has two specific strengths and two limitations. The first strength is that we will use and RCT design to test the effectiveness of ACT for the elderly. The second is its internal validity, which is protected by the structured protocol monitoring the ACT model, as well assessing the contents of the CAU by also applying the DACTS scale.

The first limitation is the fact that community mental healthcare professionals and the independent research assessor will not be blinded for which patients are included in this study. Because the only way in which independent research assessor can reach elderly people with SMI is through collaboration with the community mental healthcare professionals, it will not be possible to blind them both. The second limitation is that CAU exists of different kind of teams in different area, with different working methods. These working methods will be describe in the outcome of the DACTS but can negatively or positively affect the outcome results. In addition, the effects of ACTE will also depend on the CAU. When the quality of care of the CAU is high, there is less chance of demonstrating an effect of ACTE. This limitation is a problem in all studies comparing a new intervention with CAU [49]. Therefore, we will describe CAU thoroughly also using the DACTS, to demonstrate in what aspects ACTE and CAU differ.

The last limitation is the inclusion format. We started with the following inclusion criteria: (1) age 65 year or older; (2) having a severe mental illness, (3) no motivation for treatment, and (4) having four or more additional problems within the following domains: addiction, somatic problems, activities of daily living, housing, daytime activities, social relationships, finances, or police contacts. Untill June 2009 only 35 patients were included. Therefore we broadened our inclusion criteria by lowering the minimum age to 60 years. January 2010 only 50 patients were enrolled and we decided to limit the number of problems in several domains to 2 (was 4). Finally, in March 2010 we included only 56 patients, and then we let loose of criterion no 4. At the end of the trial by July 31 2010 we recruited 64 participants. Till August 1^st ^2010, fife patients died, 3 in the intervention group and 2 in the control group (no suicides). Because of the number of patients enrolled in this study (64 patients) the power of the study is a problem.

## List of abbreviation used

ACT: Assertive Community Treatment; ACTE: Assertive Community Treatment for the elderly; CANE: Camberwell Assessment of Needs Elderly; CAU: Care as Usual; DACTS: Dartmouth Assertive Community Treatment Scale; HoNOS: Health Of the Nation Outcome Scale; QoL: Quality of Life; RCT: Randomized Controlled Trial; SMI: Severe Mental illnesses.
